
### Blinding

Adolescents will be randomly assigned to either the intervention or control group and will not be informed about which group they are in. However, in this scenario, maintaining the blinding is not possible because participants are aware of the two different apps. Each individual will be checked to determine whether they use the GGED-AD or GGNEUTRAL app. Research team members need to be aware of which group each participant belongs to in order to guide them correctly through the application process.

### Statistical analysis

Statistical analyses will be performed using the free software R. To avoid overly optimistic estimates of the efficacy of the experiment, an intention to treat (ITT) approach will be used, using the method of the multivariate imputation by chained equations algorithm (MICE) [64].

Descriptive statistics will be used to report means, standard deviations and frequencies. In addition, tests will be performed to evaluate differences between the different variables considered in the study. To predict the different response variables under study, mixed models for repeated measures (MMRM) will be used, in which the outcomes measures are dependant variables, and the independent variables are group of the study (experimental or control), gender (male/female/other) and time (T1, T2, and T3). In addition, the baseline scores for each of the factors evaluated will be used as covariates to control that the T1 scores do not affect the results of the efficacy of the app.

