**Table 1 Tab1:**
[figure not shown]
Schedule of enrolment, allocation, intervention, and assessments within according to SPIRIT

Note. T(-1)= enrolment; T0 = allocation; T1= baseline assessment; T2 = post assessment; T3= follow-up assessment 1 month later; EDBQ = Eating Disorder Beliefs Questionnaire; EDE-Q = Eating Disorder Examination Questionnaire; BAS-2 = Body Appreciation Scale-2; PH-4 = The Patient Health Questionnaire; SISE = Single-Item Self-Esteem Scale; EDI-3 = Eating Disorder Inventory

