### Study procedure

First, an interview will be held with the school leadership team and/or heads of the guidance department of different schools in the Valencian Community, to explain the research objectives, describe the evaluation instruments, request permission to apply them, and encourage their collaboration. The schools interested in participating will distribute an information sheet specifying the objectives and characteristics of the study among the students and their families. Parents of students interested in participating in the study will have to sign the informed consent form authorizing their children to participate in the research. Students themselves must also sign it. The participants that enroll in the study will be randomly assigned by gender to the experimental and control groups using the Random.org program. On the first day of the intervention at the school center, there will be an informative session for the students to explain guidelines for their participation in the study. This will include the importance of being quiet and the option to stop participating at any time. Additionally, there will be assistance provided for the administration of the first evaluation (T1). T1 evaluation will include the evaluation instruments, and sociodemographic data, which will include information on gender, age, school, grade and academic group, height, weight. Once T1 is completed, participants will download the corresponding app to start completing the daily levels. The experimental group will use the GGED-AD app, and the control group will use the GGNEUTRAL app, named GGA and GGN respectively to avoid giving excessive information to participants. Specifically, both apps are divided into 14 blocks, and the participants will do one block each day. Each block has 4–5 levels, which is equivalent to approximately 4–5 min. During this time, members of the research group will be present in the classroom on school days, to solve possible doubts and to control the use of the application. During non-school days participants will have to complete the app at home. After completing the app, all participants will carry out the second evaluation (T2). This evaluation will be composed of the same set of questionnaires completed at T1. Once T2 is completed, the adolescents will receive instructions to not use the application until we contact them again to conduct the follow-up after one month (T3) to evaluate if the possible changes achieved are maintained over time. If someone has difficulties or feels uncomfortable during the completion of the evaluation of the module, they will be free to speak to members of the research group who, in case of it being necessary, will be referred to the school counsellor, and in addition will show them different services where they could find help for possible mental health problems.

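### The T1 score is both a modelled response and the baseline covariate in the MMRM, so the group estimate, its error rate or the fit itself can go wrong, depending on how the model is completed

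*Protocol article*

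**What the plan says.** The Statistical analysis section states one efficacy model for all outcomes: "mixed models for repeated measures (MMRM) will be used, in which the outcomes measures are dependant variables". Its terms are given as follows: "the independent variables are group of the study (experimental or control), gender (male/female/other) and time (T1, T2, and T3". The next sentence adds a covariate: "the baseline scores for each of the factors evaluated will be used as covariates". The purpose it gives is to keep the T1 scores from influencing the efficacy results.

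The note to Table 1 defines the first visit: "T1= baseline assessment". The Study procedure section says of T2 that "This evaluation will be composed of the same set of questionnaires completed at T1", so T1 and T2 are the same variable measured twice. The text names no group×time term, covariance structure or target contrast. Nothing in it takes T1 out of the response when T1 is also the covariate.

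**The concern.** A repeated-measures model can use the baseline in either of two sound ways: as a covariate for the later visits, or as the first response. The text does both. For every T1 row, the outcome and the covariate are then the same number. That row carries no information about treatment, yet it enters the group coefficient, the common baseline slope and the residual variance.

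This is the only efficacy model stated. It covers the primary outcome (EDBQ) and all secondary outcomes. At stake are the size of the reported effect, the error rate of the T2 comparison, and whether the model can be fitted at all.

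**Working it through.** **Inputs.** N = 68 is from the Sample section. Visits T1, T2 and T3 and the model terms are from the Statistical analysis section. The Expected outcomes section expects an effect at T2 that is maintained at T3. Assumed, because the article does not give them: 34:34 allocation, SD 1 at each visit, equal correlation ρ between visits (0.5 to 0.8), and an effect of 0.50 SD at T2 and T3. Missing data and the planned multiple imputation were not simulated.

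**The plan's own figure.** The stated power of 0.805 is reproduced as 0.804 with the noncentral F for multiple regression: f² = 0.15, two predictors, N = 68, λ = 0.15 × 68 = 10.2, df 2 and 65. Only N is carried forward. That 0.15 reproduces the power as f² and not as f is a separate matter.

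**(a) Listed terms only, random intercept.** With balanced data the group coefficient comes from regressing each participant's mean over the three visits on group and baseline. The T1 part of that mean is the baseline itself, so its adjusted group difference is exactly 0:

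(0 + 0.50 + 0.50)/3 = 0.33.

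Simulation with 1,000 trials per setting gave 0.325, 0.338 and 0.331 at ρ = 0.5, 0.7 and 0.8. The standard error shrinks by the same factor of 2/3, so the t statistic is that of a baseline-adjusted analysis of the T2/T3 mean. Simulated type I error was 0.056 to 0.064.

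**(b) Group×time added, pooled variance, group difference at T2.** At ρ = 0.6:

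- Common baseline slope: (1 + 0.6 + 0.6)/3 = 0.733; the right slope at T2 is 0.6.
- Residual variance at T1: (1 − 0.733)² = 0.07.
- Residual variance at T2 and at T3: 1 − 0.36 + (0.6 − 0.733)² = 0.66.
- Pooled variance: (0.07 + 0.66 + 0.66)/3 = 0.46.
- Model SE over true SE: √(0.46/0.66) ≈ 0.84.
- Type I error: P(|Z| > 1.96 × 0.84) ≈ 0.10.

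| ρ | Model SE / empirical SD (no effect) | Type I error, T2 contrast |
|---|---|---|
| 0.5 | 0.855 | 0.087 |
| 0.7 | 0.825 | 0.102 |
| 0.8 | 0.803 | 0.112 |

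**(c) Same model, T2-minus-T1 contrast.** The baseline term is the same at both visits and cancels. The contrast then has the variance of a raw change, 2(1 − ρ), where a proper baseline adjustment has 1 − ρ². At ρ = 0.6:

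- Change: SE = √(4 × 0.80/68) = 0.217, power about 0.62.
- Baseline-adjusted: SE = √(4 × 0.64/68) = 0.194, power about 0.71.

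Simulated power was 0.505 against 0.620 at ρ = 0.5, and 0.754 against 0.797 at ρ = 0.7. The contrast is valid: model SE over empirical SD was 0.96 to 1.03 and type I error 0.049 to 0.056.

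**(d) Unstructured covariance.** Set the baseline slope to 1 and the T1 intercept, T1 group difference and gender effect to 0. Every T1 residual is then 0. As the T1 variance v falls, the log-likelihood gains −(68/2) ln v, which is 34 × 2.303 = 78.3 for each factor of ten. Evaluated on one simulated data set, it went from −215 at v = 1 to −59 at 10⁻², 98 at 10⁻⁴ and 724 at 10⁻¹². There is no maximum.

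**After the change.** With T2 and T3 as responses and T1 (by time) as covariate, the T2 estimate was 0.48 to 0.51 for a true 0.50, model SE over empirical SD was 0.95 to 1.01, and type I error was 0.047 to 0.059.

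**The case against.** The strongest reply is that the harm is conditional. A reader might infer that the primary estimate or its error bars will be wrong whichever covariance structure is chosen. The documents do not support that. The hypotheses are worded as change within the experimental group and none in the control group, and the natural test of that is the T2-minus-T1 interaction contrast, which keeps its error rate. A reader might also take the loss of one third in (a) as lost evidence. It is a rescaling: coefficient and standard error shrink together, and the number misleads only if it is reported as the effect at T2. Both replies stand.

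The same goes for part of (d). In the additive model the singular solution drives the group coefficient to 0. With group×time, only the T1 difference goes to 0, and the T2 comparison becomes a change-score analysis, which is unbiased. A singular fit would also probably announce itself. Even so, a primary model should not have to rest on an unbounded likelihood.

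It can also be said that interaction, covariance structure and contrast belong in a statistical analysis plan. That is fair, and their absence is not the point here. The point is the double use of T1, which the article states.

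Finally, the three time levels might only name the visit schedule. That reading does not fit well, because "time (T1, T2, and T3" stands in a list of model terms beside "group of the study (experimental or control), gender (male/female/other".

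**Conclusion.** Wrong as written: T1 is used twice, and no way of completing the model both keeps that double use and achieves the stated purpose of the baseline adjustment. The size depends on the completion:

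- Listed terms only: the coefficient is about two thirds of the true T2/T3 effect, with a valid test.
- Group×time with pooled variance: type I error of about 0.10 for the T2 contrast (0.087 to 0.112 over the correlations tried).
- T2-minus-T1 contrast: valid, but without the precision gain from the covariate.
- Unstructured covariance: the model cannot be properly fitted.

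Only the second gives an inflated false-positive rate, and the article does not say that it is the one intended. The figures rest on the assumed correlations, the 0.50 SD effect, 34:34 allocation and complete data. The double use of T1 does not depend on any of them.

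**What to change.** Use T1 once, and say which way:

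1. Model only T2 and T3 as responses, with the T1 score and T1×time as covariates, plus gender, group, time and group×time. Name the group difference at T2 as the primary contrast.
2. Or keep T1, T2 and T3 as responses, constrain the T1 means to be equal between arms, and drop the baseline covariate. Name the T2 contrast here too.

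The T1×time term in the first option lets the baseline slope differ between T2 and T3; it goes slightly beyond removing the double use. The cost is one sentence in the Statistical analysis section. No new data are needed, and the planned 68 participants need not change on this account.

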### Data management and data monitoring

All self-report questionnaires will be completed by participants online via Lime Survey, a secure server of the University of Valencia. This server meets the security requirements of the GDPR. Participants will use a unique personal identification number (ID), so the data storage will be anonymous. The ID will be used to match the data. In addition, two control questions (e.g., “Please, answer “always” in this question”) are included throughout the evaluations to try to avoid random answers.

## Results

This study was approved by the Ethics Committee of Research in Humans of the University of Valencia on March 14, 2023, with register code 2,557,724; and accepted and published in ClinicalTrials.gov, with ID: NCT06039514. The planned data collection period is one month, and a follow-up one month later. In addition, two weeks prior to the data collection period, parents and/or guardians will be contacted to deliver the informed consent forms and collect them signed.

## Discussion

### Expected outcomes

With respect to the primary outcomes, a decrease in the degree of ascription to dysfunctional beliefs associated with eating disorders is expected in the experimental group at the T2 assessment. These changes are also expected to be maintained in the follow-up evaluation (T3) in this group. No changes are expected in the control group. The cognitive training on the adaptive and maladaptive beliefs related to ED is the principal objective of the app. Therefore, a reduction in ED dysfunctional beliefs is expected in the participants of the experimental group after the use of the GGED module, given that in other studies conducted with different modules of the GGtude platform this change was also found in the thoughts worked on (e.g., obsessive-compulsive disorder [41–43], body image [44, 45, 65], anxiety [47, 66, 67], emotional disorders [46, 68], and self-esteem [69]). Moreover, the preliminary efficacy data of GGED used in the adult population also found these changes at post-intervention [48]. It is expected that those results will be replicated in adolescents.

Regarding secondary outcomes, an increase in body satisfaction and self-esteem, and a decrease in eating symptomatology are expected in the experimental group at T2. Their maintenance is also expected at T3. None of them are expected in the control group. Changes in self-esteem and in diverse symptomatology have been found in other studies with other modules, such as obsessive–compulsive disorder [41–43] or emotional disorders [46]. With respect to body satisfaction, there are positive results [44, 45] with another module of the GGtude platform targeting body image concerns in young people (between 20 and 30 years of age). Some maladaptive beliefs worked on in this module (e.g., inflated importance of one’s appearance, perceiving the body as an object, and appearance related perfectionism) are also included in the GGED-AD module. In the same way, these results are also expected in the present study which is aimed at ED in the adolescent population. As for emotional symptomatology, no changes are expected, given that the studies with other modules have not found changes [42, 42, 48], or these were not maintained over time [65].

### Expected contribution

The GGED-AD application may be a step forward in the prevention of eating disorders in adolescents, who are at a period of greater vulnerability in their development [5, 70]. Although different adolescent eating disorder prevention programs exist, this app provides a different tool to address risk factors, given that none of the prevention programs that have been evaluated on their effectiveness are based on a mobile app. It is the first mobile application on eating disorders in Spanish based on cognitive behavioral therapy. It helps to do deeper cognitive work on the dysfunctional beliefs that develop and/or maintain these disorders. In addition, it is easy to access and use, which makes it easier to reach more people. Moreover, in the school setting, GGED will be easy to implement. A simple explanation to teachers will enable them to help and oversee its use, enhancing adherence, which is the main difficulty in the field of mobile application interventions [71, 72].

### Challenges

Some challenges that may be encountered when carrying out the study are: (1) making a schedule that interrupts the lessons as little as possible; (2) that the participants use the application properly, in silence and focused while reading the sentences; (3) that participants complete the app during weekends. In order to overcome these challenges, the researchers will meet with the team of teachers to agree on a procedure that will cause as little disruption as possible to their work. In addition, the researchers will be there every day to accompany the adolescents as they complete the app, to remind them of the importance of completing the app seriously, to see that they do not answer randomly and to encourage them to complete the app over the weekend. It is possible that the number of dropouts will be higher than expected. Thus, the goal is to motivate participants as much as possible to minimize the dropout rate.

## Data Availability

No datasets were generated or analysed during the current study

## Abbreviations

ED: Eating disorder
GGED-AD: GG Eating disorder – Adolescents
CBT: Cognitive-behavioral therapy
ID: Identification number
GGED: GG Eating disorders
EDBQ: Eating Disorder Beliefs Questionnaire
EDE-Q: Eating Disorder Examination Questionnaire
BAS-2: Body Appreciation Scale-2
PH-4: The Patient Health Questionnaire
SISE: Single-Item Self-Esteem Scale
EDI-3: Eating Disorder Inventory
